### 8.2.1 Assessment of AEs

All AEs will be assessed by the Investigator and recorded on the appropriate CRF page, including the date of onset and resolution, severity, relationship to investigational vaccine/placebo, outcome and action taken with study medication. See Appendix 2 for details of toxicity grade scales (TGS) relevant to vital signs, local reactions to injectable product, systemic signs and symptoms, systemic illness, and clinical laboratory adverse events.

In addition, injection site reactions will be graded by an Investigator or designee, according to severity. It is anticipated that the subjects may find it difficult to differentiate pain and tenderness (Norquist et. al. 2012). For this reason pain and tenderness have been combined with the following grading scale:

**Table 7 – Grading for Pain and Tenderness at injection sites**

| Mild
Grade 1                    | Moderate
Grade 2                                   | Severe
Grade 3                |
|--------------------------------------------|---------------------------------------------------------------|------------------------------------------|
| Awareness of symptoms but easily tolerated | Discomfort enough to cause interference with usual activities | inability to do work or usual activities |

For all other reported adverse events, severity should be recorded and grades as:

**Table 8 - Adverse event severity grading**

| Grade | Severity  | Comments                                                   |
|--------------|------------------|-------------------------------------------------------------------|
| 1            | Mild             | Aware of sign or symptom, but easily tolerated                    |
| 2            | Moderate         | Discomfort enough to cause interference with usual activities     |
| 3            | Severe           | Incapacitating with inability to work or perform usual activities |
| 4            | Life-threatening | Participant is at immediate risk of death                         |

A grade of severe should not be confused with a SAE. Severity refers to the intensity of an event and both AEs and SAEs can be severe. An event is defined as ‘serious’ when it meets one of the predefined outcomes as described in Section 9.3

The relationship to study product therapy should be assessed using the following definitions:

**Table 9 – Adverse Event causality assessment**

| Causality | Comment                                                                                                                                                                    |
|------------------|-----------------------------------------------------------------------------------------------------------------------------------------------------------------------------------|
| Unrelated        | AE is clearly due to extraneous causes (e.g. underlying disease, environment, known effect of another drug)                                                                       |
| Unlikely         | The temporal association between the AE and study drug is such that study drug is not likely to have any reasonable association with the AE                                       |
| Possible         | The AE could have been produced by the subject's clinical state or study drug                                                                                                     |
| Probable         | The AE follows a reasonable temporal sequence from the time of study drug administration, abates upon discontinuation of the study drug and cannot be reasonably explained by the |

| Causality | Comment                                                                                                                                                                                   |
|-----------|-------------------------------------------------------------------------------------------------------------------------------------------------------------------------------------------|
|           | known characteristics of the subject's clinical state                                                                                                                                     |
| Definite  | The AE follows a reasonable temporal sequence from the time of study drug administration, abates upon discontinuation of the study drug and/or reappears when study drug is re-introduced |

These criteria in addition to good clinical judgment should be used as a guide for determining the causal assessment. If it is felt that the event is not related to study product, then an alternative explanation should be provided.

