### 4.2 Endpoints

#### Primary endpoints:

The primary endpoints of this study are:

- Incidence and severity of adverse events in each treatment group, including vaccine related adverse events:
  - Incidence and severity of local reactions (soreness, redness, induration, ecchymosis, oedema, itching and paraesthesia) at the site of vaccination;
  - Incidence and severity of systemic reactions (fatigue, myalgia, malaise, fever, rigors, arthralgia, nausea, diarrhoea, light headedness, dizziness, hypersensitivity and headache).

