#### 6.5 Randomisation process

Subjects will first be randomized to one of 2 injection regimens using a 3:1 allocation ratio.

There will be 2 patient groups. Group 1 will be recruited first. Once this group has been fully allocated, Group 2 will open for recruitment.

Group 1 patients will receive one injection to each forearm (i.e. two injections in total at each vaccination) of either:

- Sub-group A: 15 subjects will receive 2 x 500mcg of COR-1;
- Sub-group B: 5 subjects will receive 2 x placebo.

Group 2 patients will receive two injections to the one forearm (i.e. two injections in total at each vaccination) of either:

- Sub-group C: 15 subjects will receive 2 x 500mcg of COR-1;
- Sub-group D: 5 subjects will receive 2 x placebo.

Under no circumstances are the subjects who enrol in this study are permitted to be re-randomised and re-enrolled for a second course of treatment for this protocol.

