### **6.8.3 Dosage and administration of test drugs**

Subjects are to receive either one or two intradermal injections at four week intervals for 3 vaccinations and a Booster vaccination at approximately 6 months from Baseline (see Section 6.3). Vaccinations will occur at: Baseline, Week 4, 8 and a booster will be administered at Week 24. Subjects in Group 1 will receive the intradermal injections into each forearm. Subjects in Group 2 will receive the intradermal injections to the one forearm.

Further details on the administration of study vaccine will be provided in the Study Reference Manual.

Prior to each injection, the forearm(s) that are to be injected will be examined and findings from this examination will be documented. The proposed injection site will be 5-10 cm below the elbow joint. The skin should be free from blemishes, scars, heavy hair, veins, moles, skin conditions, sores or tattoos etc. that have the potential to interfere with the detection of local injection site reactions.

Subjects in Group 2 will receive 2 injections to the same forearm, the second injection will be administered approximately 5 cm away radially, not transversely, from the first injection.

Where there is an ongoing injection site reaction an alternative site should be utilised at subsequent vaccination time points. The subsequent vaccination should be located at least 5 cm away from the previous injection site.

Intradermal injections will be carried out by an individual experienced with ID injections as per Appendix 1.

The subject will be instructed to extend their forearm(s) for 10-15 minutes after receiving their vaccination or until the bleb subsides. The injection site will be left open. No cotton wool, adhesive bandages etc. are to be applied over the injection site. The subject will be instructed to avoid touching the injected area(s).

The Investigator or nominee will make the following observations and document findings in the source notes:

- The size of the 'bleb' immediately after injecting in millimetres,
- The size of the 'bleb' during the period that the subject must keep the forearm extended,
- Whether there is an absence of a 'bleb,'
- If the injected material leaked from the skin before 15 minutes,
- If there are any unusual appearances at the injection site.

The subject will be observed for one hour following each vaccination.

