### 11.1.4 Adverse Events

The primary analysis of adverse events will consider only treatment-emergent AEs (TEAEs), events occurring for the first time, or worsening, during or after the first administration of study drug. The analysis will focus on subject incidence, although for TEAEs of special interest, the number of events may also be provided. Tables summarizing TEAEs will be displayed by preferred term and system organ class (SOC). The analysis will also include the analysis of serious adverse events (SAEs) and the categorization of AEs by severity and relationship to study drug. The analysis of AEs leading to study withdrawal or deaths on-study will also be provided in tables and/or listings. Further details will be provided in the SAP.

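### Table 9 makes Definite easier to meet than Probable, so the two top causality categories are neither ordered nor mutually exclusive, and the abatement criterion does not suit an intermittent injection

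*Protocol*

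**What the plan says.** Protocol section 8.2.1 tells assessors to grade the relationship to study product with the definitions in Table 9: Unrelated, Unlikely, Possible, Probable and Definite.

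- **Probable**: a reasonable time sequence after administration, and the event "abates upon discontinuation of the study drug and cannot be reasonably explained by the" "known characteristics of the subject's clinical state" (the row runs over a page break).
- **Definite**: a reasonable time sequence after administration, and the event "abates upon discontinuation of the study drug and/or reappears when study drug is re-introduced". The row ends there. It has no clause on other explanations.

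The sentence after the table reads "These criteria in addition to good clinical judgment should be used as a guide for determining the causal assessment".

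On dosing, section 6.8.3 says: "Vaccinations will occur at: Baseline, Week 4, 8 and a booster will be administered at Week 24".

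The grades are used in two places. The primary endpoint in section 4.2 is "Incidence and severity of adverse events in each treatment group, including vaccine related adverse events". Section 11.1.4 plans "the categorization of AEs by severity and relationship to study drug".

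**The concern.** A causality scale is useful only if each step up demands more evidence than the one below. Here the top step demands less. An assessor holding an event that meets every condition of Probable can equally code it Definite, and the table gives no rule for choosing. Two careful assessors could grade the same event differently, and neither would be wrong by the text.

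The second difficulty is the abatement criterion. It is written for a product taken continuously, where stopping removes exposure. An intradermal DNA vaccine given on four separate days cannot be withdrawn once injected, and the protocol does not say what discontinuation means between doses.

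At stake is whether the table of events by relationship can be read. A count of definitely related events is naturally taken as the best-supported evidence of a vaccine effect. Under these definitions it is not.

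**Working it through.** **Inputs.** Table 9 for the criteria and section 6.8.3 for the dosing days. Section 6.5 gives the placebo numbers: "Sub-group B: 5 subjects will receive 2 x placebo", and the same number in Sub-group D. The protocol states no figure on this point, so there is none to reproduce.

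**Step 1: write the rows as rules.** Let T = plausible timing, A = abates on discontinuation, R = reappears on re-introduction, N = not reasonably explained by the subject's clinical state.

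- Probable = T and A and N
- Definite, as written = T and (A or R)

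Four yes/no criteria give 16 combinations. The 8 with T = no meet neither row. The 8 with T = yes are:

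| A | R | N | Probable | Definite as written | Definite if and/or meant and |
|---|---|---|---|---|---|
| no | no | no | – | – | – |
| no | no | yes | – | – | – |
| no | yes | no | – | yes | – |
| no | yes | yes | – | yes | – |
| yes | no | no | – | yes | – |
| yes | no | yes | yes | yes | – |
| yes | yes | no | – | yes | yes |
| yes | yes | yes | yes | yes | yes |

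Probable is met by 2 of 16 and Definite by 6 of 16. Both Probable combinations are also Definite. Of the 4 that are Definite only, 3 have N = no, meaning that the subject's clinical state offers an explanation.

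**Step 2: try the charitable reading.** If and/or is forced to mean and, Definite is met by 2 of 16 and no longer contains Probable. The order is still not restored: timing, abatement and reappearance with another explanation present would be Definite but not Probable. Nor is this what the text says.

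**Step 3: test the abatement criterion against the schedule.** Gaps after each vaccination day, in days:

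- Baseline to Week 4: (4 − 0) × 7 = 28
- Week 4 to Week 8: (8 − 4) × 7 = 28
- Week 8 to Week 24: (24 − 8) × 7 = 112
- Week 24 to end of study at Week 48: (48 − 24) × 7 = 168

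Two readings are open.

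- *The dose-free interval counts as discontinuation.* Any event that resolves before the next dose has abated, so the criterion separates short events from long ones and says nothing about cause. With 5 + 5 = 10 placebo subjects and 4 vaccinations each, 10 × 4 = 40 placebo vaccination occasions would be open to this.
- *Discontinuation means stopping dosing*, as sections 8.6 and 10.3 use the word. A subject who stays on schedule then cannot meet A, so cannot have a Probable event, and reaches Definite only through reappearance.

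Under both readings a reaction that persists cannot be Probable, however clear the link, and can be Definite only if it reappears.

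**Step 4: follow the grades into the analysis.** Sections 8.2.2 and 8.6 act on events at least possibly related. Possible, Probable and Definite all lie on the same side of that cut, so moving an event between the top two changes neither these triggers nor the total of related events. It changes the rows of the section 11.1.4 tabulation.

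**The case against.** The strongest defence is that Table 9 is offered as a guide to be used with clinical judgment, not as an algorithm. That is fair, and it limits what can be claimed. A reader might infer that almost any short event after placebo would be graded Definite, and might attach a high percentage by assuming event durations. The documents do not support this, for three reasons:

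- Definite still requires plausible timing.
- The Unrelated row covers events clearly due to other causes, and an assessor using judgment would normally place them there. Most of the overlap between Definite and the lower rows is therefore resolved in practice.
- Any such percentage assumes that an ordinary gap between scheduled doses is discontinuation. Under the usage in sections 8.6 and 10.3 the effect runs the other way and few events would reach Probable.

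A reader might also infer that the COR-1 versus placebo contrast is distorted, or that lasting reactions are capped at Possible. Neither is shown. Vaccine administrators are kept out of assessments and other site staff, apart from pharmacy, are blinded (section 6.6). The primary adverse event analysis in section 11.1.4 covers treatment-emergent events whatever their attributed cause, and the whole analysis is descriptive. A lasting reaction can still be Definite if it reappears.

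What the defence does not do is put the categories in order. Section 8.2.1 directs assessors to these definitions, and judgment exercised on an unordered scale has nothing to settle the choice between its top two steps.

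**Conclusion.** Wrong as written. Every event that meets Probable meets Definite, because Definite omits the condition on other explanations and joins abatement and reappearance by and/or. This follows from the wording alone. The counts of 2 and 6 out of 16 describe the logic, not how often events of each kind will occur.

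The abatement criterion fails under either meaning of discontinuation, so that part does not depend on which is intended.

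The consequence is confined mainly to the split between Probable and Definite in the tabulation by relationship, and so to how the vaccine-related part of the primary endpoint is described. The at-least-possibly-related triggers are largely unaffected. No number of misclassified events can be derived from the protocol, which gives neither event durations nor a definition of discontinuation.

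**What to change.** Revise two rows of Table 9.

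- **Definite**: require all the conditions of Probable, including no reasonable alternative explanation, plus further confirmatory evidence. That could be reappearance after a later administration or, where no later dose is given, a specific feature such as confinement to the injection site. Probable is then what remains when that extra evidence is absent, so the two are ordered and exclusive.
- **Do not make reappearance mandatory.** That would bar Definite for any event first seen after the Week 24 booster, the last dose, and for any event in a subject who receives no further dose.
- **Both rows**: replace abatement on discontinuation with a criterion that suits an intermittent injection and does not depend on the event resolving, such as a clinical pattern consistent with a reaction to the injection.

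In the analysis, report relationship mainly as at least possibly related versus not, matching sections 8.2.2 and 8.6, with the five-level table as supporting detail. The analysis of all treatment-emergent events is already planned and needs no change.

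Cost: revised wording in the table and CRF, a reminder to sites, and fewer events coded Definite. The change is best made before events are coded, so that one set of definitions applies throughout.

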## 8.2.2 Adverse Event Reporting Period

All adverse events, regardless of severity, causality or seriousness must be reported from the date of informed consent until the end of the study or 28 days after the last dose of study medication, whichever is later. However, any adverse event that the Investigator believes is at least possibly related to study medication should be reported regardless of time elapsed from the final dose.

## 8.3 Serious Adverse Events

### 8.3.1 Serious Adverse Event Definition

A **serious adverse event (SAE)** is defined as follows:

Any adverse drug experience occurring at any dose that results in any of the following outcomes:

- death
- life-threatening situation (subject is at immediate risk of death)
- inpatient hospitalisation or prolongation of existing hospitalisation (excluding those for study therapy or placement of an indwelling catheter, unless associated with other serious events)
- persistent or significant disability/incapacity
- congenital anomaly/birth defect in the offspring of a subject who received study product
- Other: Important medical events that may not result in death, be immediately life-threatening, or require hospitalisation, may be considered a SAE when, based upon appropriate medical judgment, they may jeopardise the subject and may require medical or surgical intervention to prevent one of the outcomes listed in this definition. Examples of such events are:
  - intensive treatment in an emergency room or at home for allergic bronchospasm
  - blood dyscrasias or convulsions that do not result in hospitalisation
  - development of drug dependency or drug abuse

### 8.3.2 Clarification of Serious Adverse Events

Death is an outcome of an AE, and not an AE in itself. In reports of death due to “Disease Progression”, where no other information is provided, the death will be assumed to have resulted from progression of the disease being treated with the study product(s).

All deaths, regardless of cause, must be reported to Sponsor for subjects on study and for deaths occurring within 30 days of last study product dose or within 30 days of last study evaluation, whichever is longer.

“Occurring at any dose” does not imply that the subject is receiving study product at the time of the event. Dosing may have been given as treatment cycles or interrupted temporarily prior to the onset of the SAE, but may have contributed to the event.

“Life-threatening” means that the subject was at immediate risk of death from the event as it occurred. This does not include an event that might have led to death, if it had occurred with greater severity.

Complications that occur during hospitalisations are AEs. If a complication prolongs hospitalisation, it is a SAE.

“In-patient hospitalisation” means the subject has been formally admitted to a hospital for medical reasons, for any length of time. This may or may not be overnight. It does not include presentation and care within an emergency department.

The Investigator should attempt to establish a diagnosis of the event based on signs, symptoms and/or other clinical information. In such cases, the diagnosis should be documented as the AE and/or SAE and not the individual signs/symptoms.

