### 3 INTRODUCTION

#### 3.1 Disease and current treatment

Herpes Simplex Virus (HSV) type 2 is the major infectious agent that causes genital herpes (GH). Epidemiological studies estimate the incidence of acute GH infection in Europe and the United States to be between 5 and 24 cases per 100 people per year ([Malkin, 2004](#)). GH is characterised by the formation of blistering lesions associated with significant pain and discomfort. After an acute episode, the virus may persist in the body as a latent infection in dorsal root ganglia (Johnston 2011). The virus may reactivate, causing migration of virus to the mucosal surface and an outbreak of GH associated with lesion formation, pain and itching. Viral shedding may result in transmission of infection to a sexual partner (Mertz 2008). GH may also be passed from an infected mother to her new-born child in utero, peri-partum and post-partum. Most transmission occurs at the time of birth (Kimberlin 2007). In severe cases HSV infection can result in encephalitis, meningitis and even death. Genital herpes has recently been found to be strongly linked with HIV transmission in Africa ([Abu-Raddad et al., 2008](#)).

To date, treatments have failed to eradicate HSV in an infected individual. Antiviral medications have been shown to reduce the frequency, duration, and severity of outbreaks. Available drugs include acyclovir, valaciclovir, famciclovir, penciclovir, and docosanol. However, these treatments have been unable to eliminate outbreaks or completely prevent shedding. Recurrence of active lesions and asymptomatic viral shedding may therefore result in continued transmission of disease.

DNA vaccines consist of bacterial plasmids, small double strands of non-chromosomal DNA, inserted with gene sequences that encode for specific surface proteins of the target infectious agent. The plasmids typically also contain a unique promoter sequence. Injection of the plasmid into the nucleus of host cells results in transcription and translation of the gene into copies of viral proteins. The foreign antigen complexes are subsequently presented at the host cell surface allowing the immune system to detect and recognize them. A range of immune responses result, including migration of the foreign antigen: immune cell complex to the lymph node.

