## 4 OBJECTIVES AND ENDPOINTS

### 4.1 Objectives

The primary objectives of this study are to:

- Evaluate the safety and tolerability of two injection regimens of the HSV-2 DNA vaccine COR-1 compared with placebo, administered by intradermal injection as three, 4-weekly doses followed by a 6-month booster to otherwise healthy symptomatic HSV-2 positive subjects.

The secondary objectives are:

- To investigate the impact of COR-1 on:
  - Induction of an antigen specific humoral and/or cell mediated immune response against gD2.

The exploratory objectives of this study are to evaluate:

- The effect of COR-1 on HSV-2 shedding;
- The incidence of symptomatic HSV-2 genital recurrence; and
- The nature of the immunological responses to COR-1, including local tissue responses.

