### 5.3 Exclusion Criteria

1. Birthmarks, tattoos, wounds or other skin conditions on the forearms which could reasonably obscure injection site reactions.
2. Inadequate venous access to allow collection of blood samples.
3. Female subjects who are breastfeeding and those of reproductive potential with a positive urine beta human chorionic gonadotropin ( $\beta$ -HCG) pregnancy test at either Screening or the Baseline Visit (Visit 5).
4. Received immunomodulating agents (including immunosuppressive agents, interferon or other immune or cytokine-based therapies), and/or systemic chemotherapeutic agents within 60 days of Screening or expected to receive these agents during the course of the study. Stable use asthma inhalers and topical corticosteroids are permitted. All medications will be documented and reviewed for acceptance by the Investigator or a medically qualified nominee.
5. Receiving medication known to have anti-HSV-2 activity within 7 days of the Baseline Shedding Assessment.
6. History of or active serious medical or psychiatric illness which, in the opinion of the Investigator, may impair the ability to provide written informed consent and would interfere with treatment, assessment, compliance with the protocol, or subject safety.

7. History of HSV-1 genital infection, ocular HSV infection, HSV-related erythema multiforme, herpes meningitis or encephalitis.
8. HSV-1 positive PCR result during the Baseline Shedding Assessment.
9. Laboratory blood values:
  - a) Haemoglobin <12.0 grams/decilitre (g/dL) for men and <11.0 g/dL for women
  - b) Neutrophil count <1000/mm^3
  - c) Platelet count <80,000/mm^3
  - d) Aspartate aminotransferase (AST) or alanine aminotransferase (ALT) >1.5 times the upper limit of normal (ULN)
  - e) Amylase >1.5 times ULN (unless serum lipase is >1.5 times ULN)
  - f) Subjects with an estimated creatinine clearance of <80 mL/minute (min)
  - g) INR > ULN
  - h) Hepatitis B surface antigen (HBsAg), Hepatitis C Virus (HCV) antibody or HIV antibody positive.
10. Subject has received any vaccine or investigational drug within 30 days prior to Visit 2, or is due to receive subsequent vaccines during the treatment period.
11. Subject has participated in the past in another clinical trial of a vaccination related to infection with HSV (unless it can be verified that the subject received placebo).
12. Any known or suspected allergies to the study drug or its constituents.

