For any subject experiencing any event (irrespective of severity) which, in the opinion of the Investigator, contraindicates further dosing in that subject and the event is considered to be at least possibly related to treatment (or where causality to study treatment cannot be ruled out – see Section 9.2.1), continued dosing of the subject should be interrupted. In all cases, the final treatment decisions, made in response to toxicity, are the responsibility of the Investigator. A careful evaluation of the potential risk/benefit will dictate the optimal therapeutic course. Should treatment be interrupted, re-

initiation will follow review of the available safety data and in agreement with the Sponsor. There will be no dose reduction or modification.

If the Investigator deems that management of the patient's medical condition requires knowledge of the study treatment regimen, then the Medical Monitor must be contacted for consultation and the procedures described in Section 7.3 followed. If a patient dies from an event that is considered to be at least possibly related to treatment, continued dosing of all study participants should be interrupted.

Clinically significant suspected adverse drug reactions, and serious adverse events considered to be related to study procedures will be followed until resolved or considered stable. All subjects who experience a study drug related AE should be followed until resolution of the AE, even if the subject has discontinued study drug.

If an unscheduled interruption of study drug occurs, the study site should notify the Sponsor at the earliest possible time. In the event that a subject requires an unscheduled interruption of study drug under conditions other than those associated with toxicity, the case will be reviewed by the Sponsor to determine whether such a subject will be allowed to resume study drug.

Subjects withdrawn from study drug will be treated as deemed appropriate by the Investigator. Follow-up procedures should be performed and the appropriate CRFs should be completed.

The study may be terminated at any point in time at the discretion of the Sponsor.

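### Section 8.3.2 attributes a bare Disease Progression death to genital herpes by default, an assumption that does not suit this population and leans away from the causality condition in Section 8.6

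*Protocol*

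**What the plan says.** Section 8.3.2 (Clarification of Serious Adverse Events) treats death as the outcome of an adverse event. For reports that give Disease Progression as the cause, it adds that, "where no other information is provided", "the death will be assumed to have resulted from progression of the disease being treated with the study product(s".

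Three other parts of the protocol bear on what follows from that sentence:

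- **Table 9 (Section 8.2.1)** defines the causality categories. Unrelated means "AE is clearly due to extraneous causes (e.g. underlying disease, environment, known effect of another drug". Possible means "The AE could have been produced by the subject's clinical state or study drug".
- **Section 8.6** interrupts dosing of all participants under one stated event: "If a patient dies from an event that is considered to be at least possibly related to treatment".
- **Section 8.3.3.2** sends a serious adverse event to regulators as a SUSAR if it is considered possibly caused by the product and is unexpected against the Investigator's Brochure.

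**The concern.** A default cause of death makes sense where the treated disease is progressive and often fatal. Here the objectives in Section 4.1 describe "otherwise healthy symptomatic HSV-2 positive subjects". If such a subject died and the report said only Disease Progression, the protocol would supply herpes as the cause without evidence, at the point where least is known.

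What is at stake is how the death is classified, not whether it is reported. Section 8.6 makes the interruption for all participants depend on a causality judgment, and an assumed disease cause pushes that judgment towards the product not being involved. COR-1 has little human experience to set against such an assumption. Section 3.2.4 describes one earlier study of 22 volunteers, all HSV-2 seronegative, and Section 8.7 says the adverse event profile is not yet fully characterised.

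**Working it through.** No arithmetic applies. The check is to follow the text from the default to the rules that use causality.

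1. **When the default applies.** Two conditions must both hold: the report names Disease Progression as the cause, and it says nothing more. A death reported with no cause, or with any further detail, is outside the sentence.

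2. **Whether the assumed cause is plausible here.** Section 3.1 allows that HSV can kill: "In severe cases HSV infection can result in encephalitis, meningitis and even death". Section 5.2 limits entry to ages 18 to 50, and Section 5.3 excludes subjects with a "History of HSV-1 genital infection, ocular HSV infection, HSV-related erythema multiforme, herpes meningitis or encephalitis". A death from the disease is therefore possible but would be exceptional, which makes it a weak thing to assume.

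3. **Whether a relationship assessment is still required.** It is. Section 8.2 counts worsening of a pre-existing condition as an adverse event, and Section 8.2.1 has the Investigator assess relationship for every adverse event. The default does not cancel that assessment, but it fills in a cause beforehand.

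4. **Which causality category follows.** Section 8.3.2 assigns none. Two rows of Table 9 compete:
   - Unrelated gives underlying disease as its first example, which matches the assumed cause. It also requires the cause to be clear, and a cause adopted for lack of information is not clear.
   - Possible names the subject's clinical state next to the study drug, so it also fits.

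   The text below Table 9 asks for clinical judgment and for an alternative explanation when an event is called not related. The default provides that explanation ready-made. The pull is towards Unrelated, but it does not bind.

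5. **What depends on the category.** If the Investigator follows the pull, neither the interruption for all participants in Section 8.6 nor the SUSAR route in Section 8.3.3.2 is reached. If the Investigator chooses Possible, the relationship condition of both is met. Section 8.6 also has a subject-level rule that groups events whose causality cannot be excluded with those judged possibly related. The sentence on deaths does not repeat that clause.

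6. **What does not depend on it.** Section 8.3.2 sends all deaths to the sponsor whatever the cause. Section 8.3.3.1 requires a report of every serious adverse event within 24 hours regardless of causality, and provides for hospital and autopsy records of fatal events on request. Section 9 gives the Safety Review Committee unscheduled meetings when a safety concern arises, and written agreement before the first booster. Sections 8.6, 10.5 and 12.1.6 allow termination. These can act on the whole study, but none is set off automatically by a death.

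**The case against.** The strongest reply is that the sentence does little. The reporter has already named progression, and the sentence only says which disease is meant. It sets no causality category. Table 9 reserves Unrelated for clear causes and mentions the clinical state under Possible. The Investigator must try to establish a diagnosis, the sponsor can ask for records, and the committee and the termination clauses do not wait for a causality class. Together these make it hard for a trial death to stay without information for long. The committee's decision rules are in a Charter, and expectedness rests on the Investigator's Brochure; neither document is available here.

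Most of this stands, and it rules out three stronger readings that a reader might infer:

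- **That such a death could not meet the conditions in Sections 8.6 and 8.3.3.2.** The documents do not support this, because Possible remains available.
- **That the default biases the primary safety tables.** The primary endpoint in Section 4.2 is incidence and severity of adverse events by group. Relationship is a further descriptive breakdown in Section 11.1.4, and one unlikely case would not distort the whole.
- **That stopping antivirals makes the disease the one cause that must not be assumed.** Table 9 and Section 8.6 ask about relationship to the study product. A death caused by stopping antivirals would not clearly meet Section 8.6 with or without this sentence, and no section shows that COR-1 can cause severe HSV disease.

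The reply does not give the sentence a useful function in this trial. Where the report has no content, it still puts an assumption in place of an assessment.

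**Conclusion.** The point holds in a limited form. The default in Section 8.3.2 does not suit otherwise healthy adults with recurrent genital HSV-2. In the narrow case it covers, it works against the causality condition on which the protocol's one explicit, event-triggered interruption for all participants depends, and against the SUSAR route.

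The probability is low: 40 subjects aged 18 to 50, a death, this exact label, and no further information. The consequence in that one case could be large, because the classification bears on continued dosing of everyone else. The step from the default to a not-related judgment is an inference about how an Investigator would read Table 9, not a rule in the text. The conclusion also assumes that neither the Charter nor the Investigator's Brochure overrides the sentence. This is an inexpensive improvement to a safety rule, not a defect that threatens the trial's results.

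**What to change.** Delete the Disease Progression sentence from Section 8.3.2. Replace it with a statement that a report giving disease progression as the cause of death, with no further detail, carries no default attribution, and that the Investigator assesses relationship as for any other adverse event, using documents requested under Section 8.3.3.1.

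Then reconcile Table 9, Section 8.3.2 and Section 8.6, so that it is clear how a death with little information enters the causality categories and how those categories feed the interruption for all participants. The sponsor must decide which dosing rule should apply, and this change does not prescribe one.

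The cost is one sentence removed and about one added, plus a consistency read of the three places. It needs no new data, no change in sample size and no change to the analysis.
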